## Abstract

**Background:**

Major Depressive Disorder (MDD) is a prevalent mental health condition characterized by persistent low mood, cognitive and physical symptoms, anhedonia (loss of interest in activities), and suicidal ideation. The World Health Organization (WHO) predicts depression will become the leading cause of disability by 2030. While biological markers remain essential for understanding MDD's pathophysiology, recent advancements in social signal processing and environmental monitoring hold promise. Wearable technologies, including smartwatches and air purifiers with environmental sensors, can generate valuable digital biomarkers for depression assessment in real-world settings. Integrating these with existing physical, psychopathological, and other indices (autoimmune, inflammatory, neuroradiological) has the potential to improve MDD recurrence prevention strategies.

**Methods:**

This prospective, randomized, interventional, and non-pharmacological integrated study aims to evaluate digital and environmental biomarkers in adolescents and young adults diagnosed with MDD who are currently taking medication. The study implements a sensor-integrated platform built around an open-source “Pothos” air purifier system. This platform is designed for scalability and integration with third-party devices. It accomplishes this through software interfaces, a dedicated app, sensor signal pre-processing, and an embedded deep learning AI system. The study will enroll two experimental groups (10 adolescents and 30 young adults each). Within each group, participants will be randomly allocated to Group A or Group B. Only Group B will receive the technological equipment (Pothos system and smartwatch) for collecting digital biomarkers. Blood and saliva samples will be collected at baseline (T0) and endpoint (T1) to assess inflammatory markers and cortisol levels.

**Results:**

Following initial age-based stratification, the sample will undergo detailed classification at the 6-month follow-up based on remission status. Digital and environmental biomarker data will be analyzed to explore intricate relationships between these markers, depression symptoms, disease progression, and early signs of illness.

**Conclusion:**

This study seeks to validate an AI tool for enhancing early MDD clinical management, implement an AI solution for continuous data processing, and establish an AI infrastructure for managing healthcare Big Data. Integrating innovative psychophysical assessment tools into clinical practice holds significant promise for improving diagnostic accuracy and developing more specific digital devices for comprehensive mental health evaluation.

## 1 Background

### 1.1 Epidemiology of Major Depressive Disorders

Close to one billion individuals globally grapple with mental health conditions, Major Depressive Disorders (MDD) is one of the most widespread among them (Institute of Health Metrics and Evaluation, 2022). MDDs are primarily distinguished by a reduction in energy and interest in daily activities, feelings of sadness, impaired concentration, sleep disturbances, emptiness, irritability, and the presence of suicidal ideation, planning, and attempts. With over 700,000 suicides reported annually, MDD stands as the fourth leading cause of death among individuals aged 15–29 years old (Malhi et al., 2018; World Health Organization, 2022). The onset of the disease occurs during adolescence in nearly 50% of cases, and a high risk of recurrence and chronicity across the lifespan in 5% of cases. Depression is about 50% more common among women than men (Lam et al., 2016).

After experiencing a first depressive episode, the recurrence rate within 3 years is more than 30%, and some patients have recurrent episodes; thus, the course of the disease can be chronic, placing a heavy burden on both patients and society (Kuehner, 2017). Despite its high prevalence, depression remains undiagnosed and untreated in half of all cases (Kohn et al., 2004).

### 1.2 Biomarkers of MDD

The causes of MDD are complex and include multiple converging factors, such as genetic, immune system, endocrine factors, and stress-related psychosocial conditions (Ruiz et al., 2022). The specific pathways contributing to MDD onset and progression remain unclear (McIntyre et al., 2014; Lai et al., 2019; Wölfer et al., 2019), partly due to its clinical heterogeneity. MDD might have biomarkers from various sources, including inflammation, immune responses, neurotrophins, neurotransmitters, metabolic processes, and neuroendocrine systems (Belzeaux et al., 2018; Mora et al., 2018). Consequently, the use of any potential objective biomarker for accurately diagnosing depression warrants in-depth investigation.

The inflammatory immune-mediated hypothesis supported that immune dysfunction may contribute to both comorbid depression (associated with clinical inflammation) and primary depression in some individuals with low-grade inflammation indices (Averna et al., 2020). Literature data show that inflammatory biomarkers are altered in individuals with MDD (Soskin et al., 2012; Beurel et al., 2020; Osimo et al., 2020). The literature revealed significantly elevated levels of various inflammatory biomarkers, including CRP, IL-3, IL-6, IL-12, IL-18, sIL-2R, and TNFα, in individuals with MDD. Additionally, Osimo et al., observed a decreased mean-scaled variability (CVR) in patients with MDD for CRP, IL-12, and sIL-2R, indicating a more consistent inflammatory phenotype. The overall findings support the association between MDD and a pro-inflammatory state, underscoring the importance of understanding inflammation's role in shaping the clinical phenotype and affecting treatment response (Soskin et al., 2012; Beurel et al., 2020; Osimo et al., 2020).

Several studies support an important correlation between air pollution and depression. Exposure to air pollution has been found to lead to depression-like behaviors in animal studies, and exposure to environmental pollutants such as PM, PM 2.5 (Outdoor and Indoor), PM 10, CO, CO_2_, CH4 (Methane), NO_2_ (Nitrogen Dioxide), even for extended periods, which can lead to an increase or worsening of depressive symptoms (Szyszkowicz et al., 2016; Kioumourtzoglou et al., 2017; Lin et al., 2017). Air pollution has consistently been associated with increases in pro-inflammatory biomarkers in the blood and systemic oxidative stress, both involved in the pathogenesis of psychiatric disorders such as MDD (Jones et al., 2013; Buoli et al., 2018). Based on current scientific evidence (Ventriglio et al., 2021; Cuijpers et al., 2023), cumulative exposure to pollution can be measured with environmental devices essential for monitoring air quality and pollutant concentrations in the home environment. Also the prolonged exposure to air pollution may adversely affect mental health, underscoring its associations with MDD (Nobile et al., 2023). Comparing short-term and long-term exposure to environmental pollutants with the development of MDD can provide interesting data from a prognostic perspective regarding integrating technology into mental health prevention and treatment processes.

### 1.3 Digital biomarkers and MDD

Although biological biomarkers remain central in determining pathology, significant progress has been made in processing social signals as a diagnostic tool (Scherer et al., 2012; Joshi et al., 2013; Williamson et al., 2013). As a supplement to these methodologies, digital indicators of depression have the potential to contribute valuable insights to clinician evaluations. This is particularly advantageous when these indicators can be effortlessly and inconspicuously gathered outside of traditional clinical settings.

Digital biomarkers, collected through digital devices, offer objective and quantifiable physiological and behavioral data. They enable remote data collection, potentially reducing the burden of in-clinic visits and providing insights into clinically relevant changes (McIntyre et al., 2023). Wearable technologies and smartphone apps contribute to digital phenotyping, allowing for moment-by-moment assessment of individual characteristics in real-world environments. These tools have been investigated for their utility in characterizing and diagnosing MDD, including analyzing patterns of physical activity, voice samples, light exposure, and smartphone usage data (Lee S. et al., 2021; Ahmed A. et al., 2023).

The integration of digital biomarkers for depression holds the promise of improving clinical interventions (Mohr et al., 2017). This improvement can manifest through prompt identification for early intervention, continuous assessment during treatment, and the mitigation of disparities in assessment accessibility (Kumar and Phookun, 2016; Naslund et al., 2017).

Voice analytics has shown promise for detecting symptoms of depression (Soskin et al., 2012; Beurel et al., 2020).

The idea of using vocal acoustic features as potential biomarkers for identifying or diagnosing depression is an emerging area of research within the field of computational psychiatry and affective computing. The premise behind this approach is that changes in vocal characteristics, such as pitch, tone, rhythm, and intensity, may reflect underlying emotional states, including depression (Schwoebel et al., 2021; Sverdlov et al., 2021).

Several studies have explored the relationship between vocal features and depression (Mundt et al., 2012; Huang et al., 2021). These studies typically involve collecting speech samples from individuals diagnosed with depression and comparing their vocal characteristics with those of non-depressed individuals. Some common findings include:

**Pitch**: Depressed individuals may exhibit alterations in pitch, such as reduced pitch variability or overall lower pitch compared to non-depressed individuals.**Tone**: Changes in tone, including flatter or more monotone speech, have been observed in individuals with depression.**Speech rate and rhythm**: Depressed individuals may speak at a slower rate or exhibit disrupted speech rhythm compared to non-depressed individuals.**Intensity**: Variations in speech intensity, including reduced loudness or energy in speech, have been linked to depression.**Prosody**: Depressed individuals may demonstrate abnormalities in prosody, which refers to the patterns of stress and intonation in speech.

Researchers have developed computational algorithms to analyze these vocal features automatically, allowing for objective and quantitative assessment of depressive symptoms. Machine learning (ML) techniques, such as support vector machines, neural networks, and Gaussian mixture models, have been employed to classify individuals as depressed or non-depressed based on their vocal characteristics (Zhao et al., 2022).

While the potential of vocal acoustic features as biomarkers for depression is promising, several challenges remain. These include the need for large-scale validation studies, addressing confounding factors such as age, gender, and cultural differences, and ensuring the privacy and ethical use of speech data in clinical settings.

### 1.4 The role of AI in MDD

Integrating computer technologies and AI is a cutting-edge approach in mental health research (Graham et al., 2019), addressing the growing challenges faced by healthcare systems. AI, especially ML, aids in the precise and rapid diagnosis of mental health disorders by analyzing biomarkers related to patients' biological, physiological, and behavioral aspects (Iyortsuun et al., 2023). AI holds promise in understanding the complex interplay of biological, psychological, and social factors in mental health. The use of AI and wearable devices allows for continuous, objective patient monitoring, offering insights into mood changes and treatment effects, thereby enhancing mental health care and research (Nahavandi et al., 2022). Integrating AI algorithms with real-time data from wearables and sensors marks a substantial stride forward, enabling the creation of personalized and responsive mental health systems (Boucher et al., 2021; Omarov et al., 2023). Personal wearable devices like smartwatches and fitness trackers offer real-time data collection for healthcare. They are valuable in monitoring and assessing patients with depression, as they capture data related to physical activity and smartphone usage, among others. Advancements in smartphone-based speech analysis and wearable technologies like smartwatches offer new opportunities for real-life depression screening and the generation of digital biomarkers (Sequeira and Perrotta, 2020; Lee Y. et al., 2021). Research on digital biomarkers addresses four fundamental aspects: forecasting diagnostic status, evaluating symptom severity and progression, discerning treatment response, and monitoring real-world and ecological (Ahmed A. A. M. et al., 2023; Vignapiano et al., 2023). Various wearable technologies have been employed to gather physiological, activity/sleep, or subjective data in order to investigate their correlations with depression.

The next step to apply these findings clinically is to integrate relevant measures into non-invasive and cost-effective tools for use in clinical settings. This integration, including physical, psychopathological, and environmental indicators, could enhance clinical assessments by reducing inter-rater subjectivity relative to diagnosis and symptom evaluation and treatment response (McGuire et al., 2015).

Digital psychiatry integrates various healthcare aspects such as delivery, illness surveillance, disease management, and treatment, with advancements in AI and ML facilitating the translation of new data into clinically relevant digital biomarkers (Orsolini et al., 2024). Wearable devices are expected to play a crucial role in personalized telemedicine, with ongoing research aiming to enhance digital phenotyping precision and efficacy in mental healthcare, ultimately improving the quality of life for individuals with MDD (Courtet et al., 2023).

### 1.5 Aim of the study

This study focuses on evaluating specific digital and environmental biomarkers in adolescents and young adults diagnosed with MDD. The study, conducted through a prospective investigation on the MDD population (i.e., MDD), aims to:

Evaluate digital, environmental, and blood biomarkers as predictive indices of recurrence or remission of depressive pathology.Enhance digital technologies useful for predicting the severity of psychopathology and assessing treatment effectiveness.Apply technologies to distinguish individuals with depression and determine a personalized approach.Predict the severity of psychopathology among subjects using biomarkers derived from digital tools.

## 2 Methods

This project, a prospective, randomized, interventional, and non-pharmacological integrated study (Figure 1), proposes a novel technological platform designed to collect, evaluate, and analyze a comprehensive range of digital and environmental biomarkers in adolescents and young adults diagnosed with MDD, through a prospective 24 months study. The platform adheres to principles of openness, integrability, and scalability to facilitate future advancements and its main components are described in Figure 2.

**Sensor integration:** The platform utilizes a core hub capable of integrating various sensors and smart devices (wearables, smartphones, “Pothos” air purifier) to collect physiological (e.g., heart rate, oxygen saturation), behavioral (e.g., activity, sleep, voice), and environmental data (e.g., CO_2_, fine dust, environmental brightness). The platform specifically uses Android-based smartwatches and smartphones because this software allows for easier integration with experimental programs like this one.**Mobile app:** An individualized mobile application will be developed by IT.Svil. s.r.l. with the purpose of enhancing patient engagement and simplifying communication with healthcare providers. This app will facilitate the collection of self-reported data from patients, thereby streamlining the healthcare process.**Data management:** To encourage collaboration among various components, a hub-and-spoke topology will be adopted. This approach ensures efficient interaction between different entities. The utilization of commercial cloud platforms is anticipated to optimize performance, cost-effectiveness, and security. Moreover, in line with privacy by design principles, the platform will prioritize data security through measures such as secure communication channels, VPN, MFA, and data encryption and anonymization techniques.**Deep learning analysis:** The platform utilizes advanced DL algorithms to analyze the collected data. These algorithms, based on neural networks, are adept at handling complex and diverse datasets. This is crucial because the platform will gather a wide range of information such as data types (e.g., digital, environmental, and biological) and data formats both discrete and continuous. By analyzing this data, the platform aims to uncover hidden patterns that can help to: improve diagnosis and tailor treatment plans to the individual's specific needs. The focus on DL underlines the platform's aim to become a modern and innovative decision support system that goes beyond simple data analysis.**Data standardization and applications:** Data will be structured according to international healthcare standards (e.g., International Patient Summary, IPS) for clear communication and analysis. Additionally, value-added applications for data visualization beyond basic time series dashboards are envisioned. IT.Svil. s.r.l.'s IT technicians, in collaboration with the research team, will undertake the development of the data visualization dashboard. This collaborative effort will ensure comprehensive input from various team members, resulting in an efficient and effective dashboard design.

**Figure 1 F1:**
[figure not shown]
Study design.

**Figure 2 F2:**
[figure not shown]
Master data platform.

The experimental sample included 80 subjects aged 14 to 50 diagnosed with MDD (after administration of SCID-5 CV) who have been on stable medication for at least 16 weeks.

To achieve a 95% confidence level with a 5% margin of error in statistical sampling, considering a population proportion of approximately 50% and a known population size constituting 80% of the total, a minimum of 67 patients will be required. This calculation incorporates factors like the Z-score, standard deviation, and a finite population correction for larger populations. The meticulous consideration of these elements ensures the reliability and precision of the sample size, thus enhancing the credibility of the statistical findings in representing the broader population.

Participants will be excluded if they presented: intellectual disability; current or previously diagnosed psychotic disorder; mood disorder with psychotic features; bipolar disorder; alcohol and drug use with psychotropic effects according to DSM-5; pathologies of a chronic inflammatory nature; history of gastrointestinal disorders in the previous week; pregnancy.

The sample will be divided into two age groups (14–17 years and 18–49 years) and distributed in a randomized manner by random allocation in two different groups (group A and group B), each consisting of 40 subjects (10 adolescents and 30 adults).

Based on data from the Italian Statistical Institute (ISTAT) regarding the incidence of depression among italian adolescents, 20 teenager were included in the total sample.

Only the subjects assigned to group B will receive the technological equipment (Pothos system and smartwatch) for the collection of digital biomarkers; group A will be followed according to clinical standards of care. Specialized medical personnel will follow both groups from a pharmacological point of view.

The assessment will include socio-demographic information, clinical history, medication details, and various clinical scales for evaluating depression severity (HAM-D, MADRS, CDI-2) and overall functioning (GAF, C-GAS, CBCL 6–18). Clinical parameters that will be monitored daily include: heart rate, and respiratory rate, oxygen saturation, light intensity, sleep/wake rhythm, and daily step count. The daily mood will be detected by using specific emoticons by the study participants. Additionally, vocal analysis will be conducted weekly using an “*ad hoc*” app to evaluate global articulation rate, fundamental frequency, and energy during specific tasks. Specific characteristics to be analyzed include F0 range (Hz), Energy per second (mV2), Average pause duration (s), Total pause time (s), and Variability of pauses (s).

The study will also include the collection of blood and saliva samples to assess inflammatory biomarkers (IL-1β, IL-2, IL-4, IL-5, IL-6, IL-10, IL-12, and IFNγ) and cortisol levels at the beginning (T0) and the end of the study (T1). Samples of peripheral blood and saliva will be taken in the group of patients with MDD and controls.

Blood withdrawal is necessary to recover the plasma and dose cytokines of pro- and anti-inflammatory cascade; the salivary sample allows the dosage of cortisol instead. Blood (7 ml) will be collected in K_2_-EDTA tubes, and plasma will be obtained through a density gradient centrifugation using SepMate™ Tubes. According to the manufacturer's instruction, blood will be diluted with PBS and then stratified on a gradient density medium (LymphoSep™, Biowest) that will allow the separation of plasma and other components after centrifugation at 1,200 × g for 10 min at a room temperature, brake on. Plasma will be recovered and stored at −80°C until it is used.

Saliva (>1 ml) will be collected in the morning, before brushing teeth and consuming food, through the use of a Salivette^®^ (Sarstedt), a test tube containing a swab to be chewed slowly for 2 min. Salivette^®^ will be centrifuged at 1,500 × g for 10 min at 4°C and then saliva will be recovered and stored at −20°C until the use.

IL-1β, IL-2, IL-4, IL-5, IL-6, IL-10, IL-12, and IFNγ inflammatory biomarkers will be dosed in plasma through the Elisa test using ELISA Pro:Human Kits (Mabtech). IL-1α will be measured by using Interleukin-1α (human) ELISA kit (Cayman); cortisol will be quantified in saliva through a competitive assay (Cortisol ELISA Kit, Cayman). All the Elisa tests will be performed according to the manufacturer's instructions.

The study protocol and informed consent form were approved by the Campania Sud Review Board (application protocol: 48_r.p.s.o.).

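### The 67-patient minimum gives a 5% margin of error only for a closed population of about 80 people; for the broader population the margin is about 11 to 12 points

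*Protocol article*

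**What the plan says.** The only sample-size calculation in the protocol article is one paragraph in section 2 (Methods), shortly after Figure 2. It sets its target in these words: "To achieve a 95% confidence level with a 5% margin of error in statistical sampling". It goes on: "considering a population proportion of approximately 50% and a known population size constituting 80% of the total, a minimum of 67 patients will be required". Among the ingredients it lists "a finite population correction for larger populations". It closes by saying that these elements secure the reliability and precision of the sample size and make the findings more credible as a picture of the wider population.

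The same section plans 80 patients with MDD, randomised to group A or group B with 40 in each (10 adolescents and 30 adults). Only group B receives the air purifier system and smartwatch that collect the digital biomarkers.

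**The concern.** A 5-point margin at a proportion of 50% is a familiar survey target, and it usually takes close to 400 people. A figure of 67 is far below that, so the finite population correction must be doing nearly all the work. The correction shrinks the requirement that much only when the sample is a large share of a small, closed population. Yet the article ties it to large populations ("finite population correction for larger populations") and draws its conclusion about patients outside the study. The population size that would settle the matter appears only as "a known population size constituting 80% of the total", which is a fraction and not a number of people.

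At stake is the one precision statement that supports the size of the study. If the correction does not fit the population the paragraph claims to describe, the article promises a precision more than twice as good as the design can give.

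**Working it through.** **Inputs, all from the sample-size paragraph in section 2 unless noted**

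- Confidence level 95%, two-sided: z = 1.95996 (1.96 rounded).
- Margin of error e = 0.05, read as 5 percentage points.
- Proportion p = 0.50.
- Finite population correction: applied. Population size N: not given as a count.
- Stated result: 67. Planned enrolment: 80, with 40 per group (same section).

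**Step 1: size without correction**

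n0 = z² p(1 − p) / e² = 3.8415 × 0.25 / 0.0025 = 384.15, so 385 patients.

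**Step 2: reproduce the 67**

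n = n0 / (1 + (n0 − 1)/N). With N = 80:

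n = 384.15 / (1 + 383.15/80) = 384.15 / 5.789 = 66.35, rounded up to 67. This matches the article.

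**Step 3: which N gives 67?**

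Solving back, N = (n0 − 1) / (n0/n − 1). Setting n = 66 gives N = 79.5, and n = 67 gives N = 80.9. The only whole number between them is 80. The variant n0 / (1 + n0/N) gives 66.21 at N = 80 and 66.89 at N = 81, both 67 when rounded up. Under rounding to the nearest whole number the main formula points to 81. Every route leads to about 80.

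Other readings do not give 67:

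| Reading | Required n |
|---|---|
| No correction | 385 |
| N = 64 (80% of 80) | 55 |
| N = 100 | 80 |
| N = 1,000 | 278 |
| N = 10,000 | 370 |
| p = 0.8, N = 80 | 61 |
| One-sided z, N = 80 | 62 |

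**Step 4: the margin inside and outside that population**

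Inside a closed population of 80, 67 patients give

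1.96 × √(0.25/67) × √((80 − 67)/(80 − 1)) = 0.1197 × 0.4057 = 0.049, or ±4.9 points.

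This is the stated 5%. Without the correction, the half-width is 1.96 × √(0.25/n):

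| Patients | 95% half-width at p = 0.5 |
|---|---|
| 67 (stated minimum) | ±12.0 points |
| 80 (all enrolled) | ±11.0 points |
| 40 (one group, including group B with the devices) | ±15.5 points |

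**Step 5: sensitivity to the population size and to p**

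The article gives no size for the target population, so I assume a range. For a finite population of 500 to 10,000, 67 patients give ±11.2 to ±11.9 points, and 80 give ±10.1 to ±10.9. With no correction and p = 0.8 instead of 0.5, the half-widths are ±9.6 points for 67 patients, ±8.8 for 80 and ±12.4 for 40. None of these comes near 5.

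**The case against.** The strongest reply is about what the document actually says. A reader might infer that the authors used the trial's own 80 patients as the population, so that the calculation asks how many of them are needed to describe those same 80. The arithmetic makes this tempting, because planned enrolment is 80. The article does not say it. N = 80 could equally be 80% of a known list of 100 patients and match enrolment by chance; the total of 100 is my assumption, since none is stated. What can be said is that 67 needs a population of about 80, that this equals planned enrolment, and that the population is not defined. This limits how the error is described but does not remove it: a list of 80 people is not the wider population, whatever its origin.

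A second tempting reading is that remission rates or classification results are promised to within 5 points. The article attaches the margin to no endpoint. Section 3 defines remission as a HAM-D score of 7 or less and states no precision for it. Nor does the article claim a precision for the adolescent subgroups.

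A third is that 80 was a feasibility choice. That may be so, but nothing in the article says it.

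Finally, planned enrolment exceeds the stated minimum, and no analysis or decision rule shown uses the 5% figure, so correcting it changes no procedure. That stands, and it makes the repair cheap. It does not make the precision statement true, and a separate analysis plan could not make it true either.

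**Conclusion.** Wrong as written. The stated minimum of 67 follows from the stated inputs only with a population of about 80, so the 5-point margin applies to a closed list of that size. For the population that the paragraph claims to represent, the 95% half-width is about 2.4 times the stated margin with 67 patients (12.0/5) and 2.2 times with all 80 (11.0/5). For the 40 patients who supply the digital biomarkers, it is about 3.1 times (15.5/5).

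The exact half-widths rest on p = 0.5, which the article itself uses, on simple random sampling, which its formula implies, and on a target population much larger than the sample. The size of that population is an assumption, but any value from 500 upwards leaves the margin at 10 to 12 points for 67 to 80 patients.

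The conclusion does not depend on where the figure of 80 came from. It is about the stated precision, and makes no claim about power for comparing group A with group B.

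**What to change.** In the sample-size paragraph of section 2:

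1. Delete the finite-population calculation, including the minimum of 67 and the 5% margin.
2. Delete the closing claim of reliability and precision for the broader population.
3. State the true basis for enrolling 80 patients. Call it feasibility only if that was the reason.
4. Report the precision delivered. For example: *with 80 patients, a proportion near 50% is estimated with a 95% half-width of about 11 percentage points; with the 40 patients in one group, about 15.5 percentage points.*

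If the sponsor prefers to keep a finite population correction, the paragraph must name the population and give its size as a count, and the conclusion must then be limited to that population.

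The cost is a short wording amendment. Enrolment and allocation stay as they are. The only downside is that the stated precision becomes less favourable.

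### The stated sample size and ±5-point precision do not carry over to the smartwatch and Pothos data, which come from at most 40 patients, and the design supports developing an AI tool rather than validating one

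*Protocol article*

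**What the plan says.** Section 1.5 says the study focuses on digital and environmental biomarkers. Its first listed aim is to predict recurrence or remission from digital, environmental and blood markers.

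On size, 2 Methods (the sample-size paragraph after Figure 2) opens with "To achieve a 95% confidence level with a 5% margin of error in statistical sampling", assumes a proportion of about one half and "a known population size constituting 80% of the total", and concludes that "a minimum of 67 patients will be required". It adds that this secures the reliability and precision of the sample. The enrolled total is 80.

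On allocation, the same section describes groups A and B, "each consisting of 40 subjects (10 adolescents and 30 adults" in each. Then: "Only the subjects assigned to group B will receive the technological equipment (Pothos system and smartwatch) for the collection of digital biomarkers". Group A follows standard care. Blood and saliva collection is not restricted to either group.

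On analysis, the platform description in 2 Methods says: "The platform utilizes advanced DL algorithms to analyze the collected data". On the claim, the Abstract (Conclusion) says: "This study seeks to validate an AI tool". Section 4 repeats the intention to validate.

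**The concern.** The size statement covers 80 patients, but the data stream on which the study focuses exists for half of them. A reader of 2 Methods would take ±5 points as the precision of the study's main findings. For anything based on the smartwatch or the Pothos sensors, that figure does not apply. A model that combines sensor and blood markers, as the first aim suggests, is also limited to the patients who have both.

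The claim to validate makes this matter more. Daily monitoring and weekly voice tasks produce many records per patient, but the independent units for predicting remission are patients. With at most 40 of them, and no separate cohort named, the trial can build a model and check it internally. If the results were reported as a validated tool, the claim would exceed the evidence.

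**Working it through.** **1. Reproducing the 67.** Inputs from 2 Methods: 95% level (z = 1.96), margin d = 0.05, proportion p = 0.5, finite population correction.

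- Uncorrected: n0 = z²p(1−p)/d² = 1.96² × 0.25 / 0.0025 = 384.15.
- Corrected: n = n0 / (1 + (n0 − 1)/N).
- N = 80: 384.15 / (1 + 383.15/80) = 384.15 / 5.789 = 66.35, rounded up to 67. The figure reproduces.
- N = 64 (80% of 80) gives 54.98, so 55. N = 100 gives 79.51, so 80.

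Of the readings tried, only N = 80 returns 67, which treats the trial's own 80 patients as the whole population.

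**2. The same margin with 40 patients.** Half-width = z√(p(1−p)/n), multiplied by √((N − n)/(N − 1)) if corrected to N = 80.

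- n = 67, corrected: 1.96 × √(0.25/67) × √(13/79) = 0.1197 × 0.4057 = 0.049, which agrees with the stated ±5 points.
- n = 40, corrected: 1.96 × √(0.25/40) × √(40/79) = 0.1549 × 0.7116 = 0.110, or ±11.0 points.
- n = 40, uncorrected: 0.155, or ±15.5 points.
- n = 10 (group B adolescents), uncorrected: 1.96 × √(0.25/10) = 0.310, or ±31 points.

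**3. Precision of a prediction measure.** The article gives no expected AUC and no remission rate. Assumed here: AUC A = 0.75, with 20 remitted and 20 not, or 12 remitted and 28 not. Hanley–McNeil variance: [A(1−A) + (n1−1)(Q1−A²) + (n2−1)(Q2−A²)] / (n1·n2), with n1 remitted, n2 not remitted, Q1 = A/(2−A) = 0.600 and Q2 = 2A²/(1+A) = 0.6429. Hence Q1−A² = 0.0375 and Q2−A² = 0.0804.

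- 20/20: (0.1875 + 19 × 0.0375 + 19 × 0.0804)/400 = 0.00607; SE 0.078; 95% margin ±0.153.
- 12/28: (0.1875 + 11 × 0.0375 + 27 × 0.0804)/336 = 0.00824; SE 0.091; 95% margin ±0.178.

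So an observed AUC of 0.75 would be compatible with values from about 0.60 to 0.90 (20/20) or 0.57 to 0.93 (12/28), before any dropout.

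**4. Who is available for testing.** Section 1.5, 2 Methods, 3 Results and 4 Conclusions describe one cohort of 80. None names a second cohort or an external data set. For smartwatch and Pothos inputs, development and testing must therefore share the group B patients unless another document supplies others.

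**The case against.** The strongest reply is that the plan meets its own minimum: 67 are required and 80 are enrolled. That stands. A reader might infer that 40 falls short of the plan's minimum of 67, but the article ties 67 to no aim, group or data stream. The formula also adapts to whatever population is entered: with N = 40 it gives 384.15/(1 + 383.15/40) = 36.3, so 37, and 40 would pass. The figure of 67 is therefore no benchmark for prediction in either direction. What remains is that the stated precision was derived for the whole sample and says nothing about the sensor-based aim.

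A reader might also infer that group A yields no digital data at all. The text does not go that far. It confines the Pothos system and smartwatch to group B, but it does not expressly confine the voice app or the mood emoticons. Salivary cortisol and blood markers need no device.

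Finally, a reader might suppose that the analysis will split records rather than patients, or report performance on the training data. The article says neither. The validation scheme is commonly left to the full protocol or the analysis plan, which are not shown and might also name a further cohort. Its absence here is not an error. The allocation, the group-B-only equipment and the word *validate*, however, are fixed in this text.

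**Conclusion.** The point holds in a limited form. Smartwatch and Pothos data come from at most 40 patients, and the article's one size statement does not support the digital and environmental prediction aim. On the article's own inputs, the margin is about ±11 to ±15.5 points rather than ±5. For an AUC it is about ±0.15 to ±0.18, given an assumed value of 0.75 and assumed splits of 20/20 to 12/28. All of these figures take all 40 as evaluable.

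The claim to validate an AI tool goes further than a single cohort of this size can support, as long as no independent patients are named. This does not show that the planned analysis is unsound or that the recruitment target is missed. It shows that the size and the claim are stated more favourably than the allocation allows.

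**What to change.** In 2 Methods, state the number of patients and the resulting precision for each data stream: 40 for smartwatch and Pothos, and up to 80 for blood and saliva. Say whether the voice app and mood emoticons are used in group A. Do not present 67 with ±5 points as covering the sensor-based aim.

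In the Abstract (Conclusion) and 4 Conclusions, replace the claim to validate with one to develop and internally validate, unless an independent cohort is named. Add that whole patients stay together in any data split and that performance is reported with confidence intervals.

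This costs a few sentences and no extra recruitment. The downside is a less favourable claim.
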